**Figure 1 F1:**
[figure not shown]
Study design

All subjects will undergo a baseline assessment and re-assessment at 12 and 24 weeks. Following baseline assessment, stratified randomisation to the exercise or control group will be performed. Permuted block randomisation with block sizes of 4 will be used [29]. In order to achieve groups balanced for exercise capacity, subjects will be stratified based on the peak VO_2 _> or ≤ 70% of predicted values [30].

Subjects in both groups will receive usual medical care. Subjects randomised to the exercise group will undergo a 12 week, individually prescribed, supervised, outpatient exercise training program, followed by a 12 week home exercise program.

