### Sample size calculation

Improvements in endurance time following exercise training have recently been reported in the PAH population [10]. These authors [10] reported a mean increase in endurance time, as measured from a constant workload cycle ergometer test, of 270 seconds. The constant workload tests were set at 75% of the peak workload achieved during the incremental CPET, which is consistent with our study's protocol. The mean endurance time (standard deviation) at baseline and post-training were 390 (40) and 660 (60) seconds respectively.

Conservative sample size calculations have been performed using a two-sided Mann-Whitney U test, assuming that the actual distribution is a double exponential. Group sizes of 14 will achieve 91% power to detect a difference of 200 seconds between the null hypothesis that both group means are 600 seconds and the alternative hypothesis that the mean of group 2 is 400 seconds with estimated group standard deviations of 180 and 120 and with a significance level (alpha) of 0.01.

A total of 34 subjects (17 in the exercise group and 17 controls) will be recruited to allow for 20% attrition of subjects from the per protocol analysis.

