### Statistical methods

Data will be analysed using SPSS software (Version 17.0; SPSS Inc; Chi). Data that are not normally distributed will be transformed and if transformation fails to satisfy normality, non-parametric tests will be used. The primary and secondary outcomes in the exercise and control groups will be compared using two-way analysis of variance to account for group and time interactions. Statistical relationships between outcome variables will be analysed using Pearson's or Spearman's correlations as appropriate. Data will be analysed using (i) per protocol analysis and (ii) intention-to-treat analysis. Per protocol analysis will be restricted to the data from subjects who complete all assessments and for the exercise group who attend at least 75% of their exercise classes. The required number of sessions must be achieved within a period of 15 weeks for both the supervised and home exercise training programs, allowing for intercurrent illness and other factors that may impact on an individual's ability to attend sessions. The last-observation-carried-forward method will be used to impute missing data at 12 and 24 weeks for the intention-to-treat analysis [41]. The Berger-Exner [42] test will be carried out to determine whether selection bias has been introduced into the study.

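### The sample size protects a per-protocol set that is not a randomised comparison, neither analysis set is named as deciding, and the 15-week session window is not reconciled with assessments at 12 and 24 weeks

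*Protocol article*

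**What the plan says.** **Sizing.** Sample size calculation states: "Group sizes of 14 will achieve 91% power to detect a difference of 200 seconds". The calculation is described as "using a two-sided Mann-Whitney U test, assuming that the actual distribution is a double exponential", and its remaining inputs are given as "with estimated group standard deviations of 180 and 120 and with a significance level (alpha) of 0.01". The recruitment target is then set: "A total of 34 subjects (17 in the exercise group and 17 controls) will be recruited". The reason given for going from 14 to 17 per group is "to allow for 20% attrition of subjects from the per protocol analysis".

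**Analysis sets.** Statistical methods lists per protocol as (i) and intention-to-treat as (ii) and ranks neither. The per-protocol set is "restricted to the data from subjects who complete all assessments and for the exercise group who attend at least 75% of their exercise classes". The intention-to-treat analysis fills missing 12- and 24-week values by last observation carried forward.

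**Withdrawal.** Withdrawal Criteria takes subjects out of the study when two or more signs of clinical worsening are present. Outcomes lists worsening clinical status as a secondary outcome, and adverse events leading to withdrawal as part of a primary one.

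**Timing.** Under Recruitment and Randomisation: "All subjects will undergo a baseline assessment and re-assessment at 12 and 24 weeks". The Abstract gives the same times, and each programme is described as lasting 12 weeks. Statistical methods adds: "The required number of sessions must be achieved within a period of 15 weeks for both the supervised and home exercise training programs".

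**The concern.** The question is one of superiority: does exercise training improve exercise capacity and quality of life over usual care? Randomisation protects that comparison only while subjects are analysed as allocated. Here the number recruited is justified by the set that abandons this protection, and if the two analyses disagree the text does not say which one answers the question.

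The set loses subjects in three ways that may be related to outcome:

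- Exercise subjects below the attendance threshold leave, while comparable controls stay.
- Subjects withdrawn before week 24, including those who deteriorate, leave from either arm.
- Subjects with a valid 12-week result leave if they miss week 24, although the first hypothesis concerns the 12-week programme.

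The timing rule raises a second problem. If sessions may continue after the date on which the outcome is measured, either per-protocol status depends on attendance after the outcome, or assessments move later for some exercise subjects with no matching rule for controls.

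**Working it through.** **1. The plan's own figure.** Inputs from Sample size calculation: 14 per group, difference 200 s, SDs 180 and 120 s, two-sided alpha 0.01. The usual Mann-Whitney adjustment for a double exponential divides n by 2/3, giving an effective 14 / (2/3) = 21 per group.

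- Standard error = √(180²/21 + 120²/21) = √(46,800/21) = 47.2 s.
- Noncentrality = 200 / 47.2 = 4.24.
- Power from the noncentral t with Welch degrees of freedom = 92.7%, against 91% stated.

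This reproduces the figure closely enough. It relies on a large-sample adjustment: direct simulation of the Mann-Whitney test gave about 79% at 14 per group and about 90% at 17. That is a separate matter, and the power figures below stay on the plan's own basis.

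**2. The attrition step.** 14 × 1.2 = 16.8, rounded to 17 per arm, 34 in total. Dividing instead, 14 / 0.8 = 17.5, rounded to 18 per arm, 36 in total. The gap of 2 is small and is not the point. What matters is that the 20% is defined as loss from the per-protocol set, so it mixes missed assessments (both arms) with poor attendance (exercise arm only).

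**3. Who leaves the per-protocol set.**

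| Subject | Exercise | Control |
|---|---|---|
| Attends under 75% of classes | excluded | no such rule |
| Withdrawn before week 24, for worsening or otherwise | excluded | excluded |
| Has 12-week data, misses week 24 | excluded | excluded |
| Worsening first found at the week-24 visit, all assessments done | retained if attendance met | retained |

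The first row operates in one arm only. The second and third act in both arms, but their effect depends on how many leave each arm and why.

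**4. Power if the as-allocated analysis decides.** Assumption: a fraction f of the exercise arm gains nothing and the SDs do not change. Then the difference is 200 × (1 − f). With 17 per arm, effective n = 17 × 1.5 = 25.5 and the standard error is √(46,800/25.5) = 42.8 s.

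| f | Difference | Power at 17 per arm | Per arm for 91% power |
|---|---|---|---|
| 0 | 200 s | 97% | 14 |
| 10% | 180 s | 93% | 17 |
| 20% | 160 s | 84% | 21 |
| 30% | 140 s | 71% | 26 |

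These are analysed numbers, before any allowance for missing outcomes.

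**5. The session window.** Two 12-week programmes (12 + 12 = 24 weeks) do not fit into a single 15-week period, so the rule must mean 15 weeks for each.

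- First assessment: 15 − 12 = up to 3 weeks past it.
- Second assessment, home window opening when a 15-week supervised window closes: 15 + 15 = 30, and 30 − 24 = up to 6 weeks past it.
- Second assessment, home window opening at week 12: 12 + 15 = 27, up to 3 weeks past it.
- Second assessment, home window opening with the first home sessions in the last 4 weeks of supervision (about week 8 or 9): it closes at about week 23 or 24, so there is little or no overrun.

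The text does not say which applies. The 75% threshold is stated for classes only, so the number of home sessions required is not fixed either.

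**The case against.** The strongest reply is that an intention-to-treat analysis of the same outcomes is already planned and includes every subject the per-protocol set loses. Being listed first does not make a set primary, and an attendance rule can only apply to the arm that has classes. All of this is correct, so a reader should not infer that an as-allocated analysis is absent or that per protocol has been declared primary. What stands is that the sample size is tied to the per-protocol set and nothing says which result decides. The planned intention-to-treat analysis also carries the last value forward, so a subject withdrawn for worsening may be represented by a baseline value.

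Four stronger readings are tempting but not supported:

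- *A fixed inflation of the effect.* With a pooled SD of √((180² + 120²)/2) = 153 s, if the 20% removed scored 1 SD lower, the shift would be 0.20 × 153 = 31 s, or 15% of 200 s. The 1 SD is not in the document, the 20% covers losses in both arms, and a stable difference in level would largely cancel in a group-by-time analysis. Bias needs excluded subjects to have changed differently. An illustration with no true effect, SD 150 s and assumed attendance-outcome correlations of 0.3 to 0.5 gave 13 to 23 s with 3 of 17 dropped and 20 to 35 s with 5 of 17. At zero correlation it gave none. These figures show sensitivity to assumptions and do not estimate the bias in this trial.
- *The trial cannot show worsening.* Worsening and adverse-event withdrawals are outcomes in their own right. The efficacy means under-represent worsening, but the trial still records it.
- *Everyone withdrawn for worsening is lost.* Subjects whose worsening is first found at the week-24 visit have completed all assessments.
- *The whole exercise arm is tested 3 to 6 weeks late.* These are upper limits for some subjects. If 75% of 36 classes (27) is what is required, it takes 9 weeks at 3 per week, so only those short of it at week 12 would use the extension. Assessment visits already spread over up to 2 weeks, and the 6 weeks needs the windows to run end to end.

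**Conclusion.** The concern holds in bounded form. The sample size is justified by a non-randomised set and the deciding set is not named. That set excludes on attendance in one arm, on withdrawal before week 24, and on a missed week-24 visit even where 12-week data are sound. It can bias the efficacy comparison. The attendance filter plausibly favours exercise, but the net direction and size depend on how excluded subjects would have changed and which arm loses more, and the document gives no figure for either.

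The session window and the assessment times are unreconciled as written. The overrun is up to 3 weeks at the first assessment, and between roughly none and 6 weeks at the second depending on when the home window opens.

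Making the as-allocated analysis primary costs little power if non-attendance is light (93% at 10% dilution) and more if it is substantial (84% at 20%, 71% at 30%). These figures assume that non-attenders gain nothing, SDs are unchanged, all 17 per arm contribute outcomes, and the plan's large-sample power method applies.

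**What to change.** - Name the as-allocated analysis of all randomised subjects primary, with per protocol supportive.
- For the 12-week per-protocol comparison, require only the 12-week assessment.
- Reconcile Recruitment and Randomisation with Statistical methods: time both assessments from randomisation with the same window in both arms, and count towards per-protocol status only sessions attended before the assessment concerned. State when the home window opens and which session count applies to the home programme.
- Restate the 20% as loss of outcome data, and check power on the as-allocated basis for a plausible range of non-attendance.

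The cost is mainly wording. The headline estimate will include poor attenders and may be smaller, with lower power if non-attendance is substantial. Holding 91% power would need 21 analysed per arm at 20% dilution, on the assumptions above.

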(ii) Exercise training is safe and improvements in exercise capacity will be achieved without evidence of clinical worsening

(iii) An additional 12 week home exercise program will maintain or further improve the benefits gained during the 12 week, supervised, outpatient program.

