### Withdrawal Criteria

Subjects will be withdrawn from the study if they demonstrate deterioration in their clinical status (time to clinical worsening), defined by the presence of two or more of the following [38,39]: (i) escalation of medical therapy (increased dose of medication or commencement of intravenous epoprostenol); (ii) deterioration (≥ 1) in WHO functional class; (iii) development of right heart failure (as indicated by increased jugular venous pressure, new/worsening hepatomegaly, ascites or peripheral oedema); (iv) resting echocardiogram changes (deterioration in right ventricular size and function, right atrial size, pulmonary arterial systolic pressure (PASP) and, where PASP cannot be determined, pulmonary acceleration time); (v) oedema that does not respond to oral diuretics; (vi) hospitalisation for PAH; (vii) listing for transplantation; (viii) ≥ 20% deterioration in 6MWD (ix) progressive worsening of dyspnoea at rest or on exertion over the past 3-5 days [40]; (x) deterioration in ventilatory efficiency (V_E_/VCO_2_) reflecting worsening gas exchange.

Subjects may also be withdrawn from the study at their request or if they experience a serious adverse event during or up to 24 hours following an exercise training session and it is deemed unsafe to continue participation by the treating medical officer from the Royal Perth Hospital Pulmonary Hypertension Service. Adverse events comprise: (i) an incident requiring a medical emergency team call (according to Royal Perth Hospital criteria); (ii) exercise-related incident requiring presentation to the Emergency Department or General Practitioner; (iii) hospital admission due to PAH or worsening right heart failure; (iv) an incident resulting in the patient ceasing exercise during class (chest pain, syncope, worsening dyspnoea despite rests, hypotension/hypertension, bradycardia/tachycardia (as measured by a polar monitor and confirmed by palpation), nausea (associated with sweating, pallor and/or tremor), vagueness, vasovagal, arrhythmia); (v) death.

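### Subjects who clinically worsen are withdrawn and then imputed by LOCF, which fixes the 12-to-24-week change at zero for those lost after week 12 and partly supplies the maintenance result

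*Protocol article*

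**What the plan says.** Four statements in the protocol article combine.

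- Withdrawal Criteria: "Subjects will be withdrawn from the study if they demonstrate deterioration in their clinical status", with deterioration "defined by the presence of two or more of the following" in a list of ten. The list includes "≥ 20% deterioration in 6MWD", a fall in WHO functional class, worse ventilatory efficiency, escalation of therapy, right heart failure and hospitalisation for PAH. Subjects may also be withdrawn "if they experience a serious adverse event during or up to 24 hours following an exercise training session", if the treating medical officer judges it unsafe to go on.
- Recruitment and Randomisation (text below Figure 1): "All subjects will undergo a baseline assessment and re-assessment at 12 and 24 weeks". No assessment after withdrawal is described.
- Statistical methods: "The last-observation-carried-forward method will be used to impute missing data at 12 and 24 weeks for the intention-to-treat analysis". The only other analysis is per protocol, limited to subjects with all assessments and, in the exercise group, at least 75% class attendance.
- Background, hypothesis (iii): "An additional 12 week home exercise program will maintain or further improve the benefits gained during the 12 week, supervised, outpatient program".

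Under Outcomes, adverse events leading to withdrawal belong to primary outcome (v), and worsening clinical status is secondary outcome (iv).

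**The concern.** The withdrawal rule makes data missing because the subject got worse, and the imputation rule then fills the gap with the most recent earlier value. When the worsening falls between visits, that value was recorded before it. An exercise subject who does well at week 12, worsens at week 18 and is withdrawn enters the 24-week comparison with the week-12 result unchanged.

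Zero change from 12 to 24 weeks is what maintenance means in hypothesis (iii), so for these subjects the imputation supplies the answer instead of testing it. The intention-to-treat analysis is the only one that keeps every randomised subject. The per-protocol analysis removes the same people, so agreement between the two would not be reassuring. With 17 per arm, a few such subjects can move the arm mean by an amount that matters.

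**Working it through.** **Inputs from the protocol article (Sample size calculation).** Design means 600 s and 400 s for endurance time, a difference of 200 s; 14 per group needed, 17 per group recruited.

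**The plan's own figures.** The plan gives no figure for the effect of LOCF. Its attrition figure reproduces closely: 28 × 1.2 = 33.6, rounded to 34 (dividing gives 28 / 0.8 = 35). The planned loss per arm is 17 − 14 = 3. The stated 91% power plays no part below. For the record, a t calculation with the group size scaled by the rank test's efficiency of 1.5 (14 to 21) gives 0.927, and direct simulation of the rank test gives 0.79 to 0.81.

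**Assumptions, not in the document.** At week 12 exercise subjects are at 600 s and controls at 400 s, the latter also being baseline. Completers do not change afterwards. Three subjects in an arm worsen after week 12 and are not assessed at week 24. Their true 24-week value is 400, 320 or 240 s, that is 0, 20 or 40% below baseline. Three is the whole planned loss, and that allowance also covers poor attendance, so it is an upper illustration and not a forecast of worsening.

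**Formulas.** True exercise mean at week 24 = (14 × 600 + 3 × v) / 17, where v is the true value of those lost. The LOCF mean is 600 s whatever v is.

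- v = 400: 9600 / 17 = 564.7 s
- v = 320: 9360 / 17 = 550.6 s
- v = 240: 9120 / 17 = 536.5 s

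So the true within-arm change from week 12 is −35.3, −49.4 or −63.5 s, and LOCF reports 0. With only 1 exercise subject lost, the true mean is 588.2, 583.5 or 578.8 s.

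For controls, the true mean is (14 × 400 + 3 × v) / 17: 385.9 s at v = 320 and 371.8 s at v = 240.

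**Group difference at week 24**

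| Lost after week 12 | v (s) | LOCF (s) | True (s) | LOCF minus true (s) |
|---|---|---|---|---|
| 3 exercise, 0 control | 400 | 200 | 164.7 | +35.3 |
| 3 exercise, 0 control | 320 | 200 | 150.6 | +49.4 |
| 3 exercise, 0 control | 240 | 200 | 136.5 | +63.5 |
| 0 exercise, 3 control | 320 | 200 | 214.1 | −14.1 |
| 0 exercise, 3 control | 240 | 200 | 228.2 | −28.2 |
| 3 in each arm | same v in both arms | 200 | 164.7 | +35.3 |

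**Timing.** If the 3 exercise subjects are lost before week 12, baseline is carried and the LOCF difference is (14 × 600 + 3 × 400) / 17 − 400 = 164.7 s. That credits them with no benefit but still hides any fall below baseline: LOCF overstates the difference by 0, 14.1 or 28.2 s for v = 400, 320 or 240. With 3 lost in each arm before week 12 and the same v, the bias is 0.

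**Would a likelihood-based model be enough?** Assume 20% of the exercise arm is lost after week 12 and would decline 200 s, while completers decline 50 s. The true mean change is 0.8 × (−50) + 0.2 × (−200) = −80 s. LOCF gives 0.8 × (−50) + 0.2 × 0 = −40 s. A missing-at-random model, with similar week-12 values in both subsets, projects the completers' −50 s onto those lost and gives about −50 s. It recovers about 10 of the 40 s.

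**The case against.** Most of the case on the other side stands as a limit on the point.

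- A reader might infer that every worsening subject enters the analysis as unchanged. The documents do not support that. The walk test and the incremental exercise test are scheduled only at the three assessments, so worsening picked up by them at week 12 is already in the carried value, and results obtained at week 24 need no imputation. The problem is confined to worsening between visits with no later assessment, such as a hospital admission or escalation of therapy.
- A reader might infer that LOCF always favours exercise. It does not: the rule covers both arms, and the table shows the group difference biased either way.
- A reader might infer that harm is hidden from the trial. It is not, because withdrawals for adverse events and clinical worsening are outcomes in their own right. What is masked is the deterioration within the exercise-capacity and quality-of-life comparisons.
- The overlap between withdrawal triggers and outcomes is limited to secondary outcomes: walk distance, WHO class and, at isotime only, ventilatory efficiency.
- LOCF also treats copied values as observed, but its net effect on the standard errors was not worked out and no weight is put on it.

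What remains is that the imputation method is fixed in the text, so it is not a detail left to a later plan, and no stated analysis checks it.

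**Conclusion.** The point holds for subjects who worsen between visits and have no later assessment. If they are lost after week 12, LOCF sets their 12-to-24-week change to exactly zero and biases the within-arm result towards maintenance. The group difference may be biased in either direction. In the illustration it is 200 s by LOCF against a true 165, 151 or 136 s when 3 of 17 exercise subjects are lost, and it is understated by 14 to 28 s when only 3 controls are lost and fall 20 to 40% below baseline.

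The number lost, their timing and their true values are assumptions; only the 600 and 400 s means and the group sizes come from the protocol article. If few subjects worsen between visits, the effect is small. This should be fixed, but it does not undermine the trial as a whole, because worsening is reported separately.

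**What to change.** - **Statistical methods, main analysis.** Replace LOCF with a likelihood-based repeated-measures model using all observed visits, with group by visit, baseline value and the randomisation stratum (peak VO2 above, or at or below, 70% of predicted).
- **Statistical methods, sensitivity analysis.** That model assumes data are missing at random, which withdrawal for worsening is likely to violate. Pre-specify a sensitivity analysis in which subjects withdrawn for clinical worsening receive an unfavourable value, by worst rank or by reference-based imputation. It should include all randomised subjects.
- **Withdrawal Criteria.** Reconcile this section with the intention-to-treat aim by separating withdrawal from data collection. Outcomes that can still be obtained, such as questionnaires, WHO class and events, should be collected at 12 and 24 weeks in both arms. The clinical criteria are not in question here, and decisions on training and exercise testing stay with the sponsor and the treating physicians.

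The cost is a few sentences of text, slightly more analysis work and a few follow-up contacts. The data-collection change is the urgent one, since outcomes not collected at the time cannot be recovered.
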